### Recruitment

To reach the number of patients needed to conduct the study with enough power, all hospitals in Sweden with patients acutely ill in COVID-19 are invited to participate.

### Measurements

Blood samples for analysis of the following routine blood chemistry will be taken prior to start of treatment if available at respective study sites: C-reactive protein, procalcitonin, white cell count, haemoglobin, creatinine, creatine kinase, D-dimer, troponin, Alanine aminotransferase (ALT), Aspartate aminotransferase (AST), Lactate dehydrogenase (LD) and bilirubin.

Blood samples for detection of SARS-CoV-2 in the blood will be taken prior to treatment start, daily during treatment and until two consecutive negative results are obtained. Serological samples will be collected for subsequent SARS-CoV-2 culture whenever PCR samples are taken.

### Data collection

The following basic data will be collected and entered into electronic records (REDCap):

Age, gender and reason for non-inclusion for screened but not included patients.Date of symptom onset and date of start of CP therapy will be recorded and used in subgroup analyses.Basic patient characteristics, comorbidities, disease severity characteristics and treatment on study entry.Each dose of CP and date it was given along with any observed AEs.Concomitant treatment with antivirals and/or corticosteroids.The outcome of daily SARS-CoV-2 PCR until two consecutive negative PCRs are recorded.The need for mechanical ventilation and date when this was initiated.For patients not eligible for intensive care: each day when PaO_2_/FiO_2_ ratio was less than 70 for ≥12 hours. PaO_2_ and FiO_2_ will be estimated from SO_2_% and O_2_ flow in nasal cannula, face mask or face mask with reservoir based on medical record data. A ratio of 70 is approximately equal to 90% SO_2_ with 8–9 L of oxygen flow using a face mask with a reservoir.Date of death.Survival or death by day 28 and day 60.

Data are entered directly into a computerised system that includes automatic range checks.

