## Introduction

COVID-19 is an ongoing pandemic caused by the SARS-CoV-2. Current treatment options are limited. Corticosteroid therapy (dexamethasone, hydrocortisone or methylprednisolone) for up to 10 days has been shown to significantly reduce mortality in severely ill patients with COVID-19, summary OR 0.66 (95% CI 0.53 to 0.82).^1 2^ Dexamethasone also reduced the risk of progression to invasive mechanical ventilation (relative risk 0.76 (0.61–0.96), p=0.021). However, no improvement was seen in patients not requiring supplemental oxygen therapy and corticosteroids were associated with prolonged viral shedding.^1 3 4^

Convalescent plasma (CP) therapy is a form of immunotherapy that has been used for the treatment and prevention of infectious diseases for more than 100 years. CP was successfully used in the treatment of SARS, Middle East respiratory syndrome and the 2019 H1N1 pandemic.^5–8^ A meta-analysis of 32 SARS and severe influenza studies showed that CP treatment was associated with a significant reduction in the pooled odds of mortality (OR 0.25; 95% CI 0.14 to 0.45).^9^ However, CP treatment did not significantly improve the survival of patients with Ebola disease.^10^ This was possibly due to a lack of data on neutralising antibody titres.

Early studies on CP therapy suggested that in COVID-19, CP should be given daily until the patient becomes virus free.^11–14^ In America, more than 70 000 patients have received CP. A safety report on 20 000 patients indicated that CP was well tolerated and not associated with severe adverse events (AE).^15^ In a cohort of 1000 patients, mortality was significantly lower in patients receiving CP with antibody titres ≥1/640 compared with patients receiving CP with lower titres if the treatment was initiated within 72 hours of admission (data available at www.fda.gov). Though the numbers treated are large and the results suggest a beneficial effect, the lack of controls leaves space for much uncertainty. Moreover, there are randomised studies reporting no beneficial effect, although CP therapy was not specifically given to patients with viraemia in these trials.^16–18^ There is thus a need for a randomised clinical trial that focuses on a population at high risk of severe COVID-19 (ie, patients with viraemia in early disease) and on which plasma to give and how (preferably neutralising antibodies of at least 1:640 and one plasma bag infused daily until clearance of viraemia occurs).

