### Rationale

CP has been shown to be safe and effective for treatment of several diseases. Data indicate that it is safe for treatment of COVID-19. Preliminary data indicate that treatment should be given early prior to development of severe illness. A group at high risk of severe disease and death that has the most to benefit from CP can be easily identified by detection of viraemia on admission.^19^ Phase II study data indicate that treatment should be given until SARS-CoV-2 is no longer detected in serum and the donor antibody neutralisation titres should be ≥1/640. A randomised controlled trial in which patients with viraemia are treated with CP with the equivalent of an antibody titre ≥1/640 is thus required to determine if CP can be an effective COVID-19 treatment.

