## Methods and analysis

### Study design

A multicentre, open 2:1 randomised controlled clinical trial conducted in Sweden. Study sites include Karolinska University Hospital, Danderyd Hospital and the Hospital in Falun (for a complete list of study sites, visit ClinicalTrials.gov). All Hospitals with infectious diseases departments in Sweden have been invited to participate. The study will be conducted in accordance with the Helsinki Declaration on ethical principles for medical research involving human subjects. The study is expected to take place during 2021 (3 December 2020 to 1 February 2022). This study protocol is prepared using the Standard Protocol Items: Recommendations for Interventional Trials guidelines.^21^

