### Intervention

Patients will be randomised 2:1 to treatment with CP plus standard care or standard care only. Randomisation is by random permutated blocks using REDCap or equivalent.

Participants will receive 200 mL CP daily until SARS-CoV-2 is no longer detectable in the blood up to a maximum of 10 CP infusions. CP will be given as a slow infusion over 2 hours. CP neutralisation titre of ≥1/640 (which is higher than conventionally used as high-titre plasma) or an ELISA reactivity against the Spike protein of SARS-CoV-2 by the Euroimmun commercial assay >9 is desired. The in-house neutralisation test is performed as described.^22^

New antibody tests are under development and can be used instead if equivalence to neutralisation or Euroimmun ELISA is demonstrated. If no high-titre plasma is available, lower antibody titre plasma may be given but must in no instance be lower than 4 in the Euroimmun ELISA. CP will be obtained from respective study sites blood bank. If this is not possible, CP will be available from the Department of Clinical Immunology and Transfusion Medicine at Karolinska University Hospital.

Patients will be monitored for AEs, especially allergic reactions and impaired renal function. Patients not able to receive study treatment will receive standard care.

If an attending physician assesses that a patient is suffering from an AE induced by the plasma infusion and requiring treatment, the infusion will be stopped for that patient. The outcome will be classified as an AE necessitating treatment stop.

A study subject can terminate his/her participation in the study at any time without giving a reason why. Should a subject wish to do so, he/she will be treated in line with standard recommendations.

Study organisers can end a patient’s participation for safety reasons.

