### Outcomes

Primary endpoint: mortality by day 28 after inclusion into the study.

Secondary endpoints:

Mortality by day 60 after inclusion into the study.Requirement of invasive ventilation or PaO_2_/FiO_2_ ≤70 for ≥12 hours in the case of patients not eligible for intensive care.AEs.Dose of plasma needed to clear viraemia.Time to clearance of viraemia.

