### Sample size

Available data indicate that CP is safe and that high-titre CP can reduce mortality by approximately 30%. For that reason, a 2:1 randomisation is preferred. Randomisation will be done by computer-generated random numbers. Based on the available data, we assume 85%–88% survival in the control arm. Assuming a power of 80% and an alpha of 0.05%, 920 patients need to be enrolled.

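### Subgroups that use the date of first convalescent plasma have no control counterpart; timing should be counted from symptom onset to randomisation in both arms

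*Protocol article*

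**What the plan says.** In the protocol article, the list under Data collection includes this item: "Date of symptom onset and date of start of CP therapy will be recorded and used in subgroup analyses". No outcome, cut-point or comparator is attached to it, and no reference date is named for controls.

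The statements that bear on it are these:

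- **Intervention:** "Patients will be randomised 2:1 to treatment with CP plus standard care or standard care only". The same section adds: "Patients not able to receive study treatment will receive standard care".
- **Study design:** "A multicentre, open 2:1 randomised controlled clinical trial conducted in Sweden". No control infusion is described.
- **Outcomes:** "Primary endpoint: mortality by day 28 after inclusion into the study".

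Timing also matters to the trial's argument. The Rationale says: "Preliminary data indicate that treatment should be given early prior to development of severe illness". The Introduction cites an uncontrolled external cohort in which higher-titre plasma did better than lower-titre plasma "if the treatment was initiated within 72 hours of admission".

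**The concern.** A subgroup analysis in a randomised trial is protected by randomisation only if membership can be determined in both arms from information fixed before allocation. The date of symptom onset meets that condition. The date of first CP does not: controls have none, CP-arm patients who never start have none, and for the others it is settled after allocation by events that may be related to prognosis.

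The sentence names the two dates together, so the interval from onset to first CP is a natural variable to build from them. That interval has the same defect.

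What is at stake is the answer on timing of treatment. If it rests on the CP start date, a difference between earlier and later starters could reflect who started when, and who lived long enough to start, rather than an effect of plasma.

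**Working it through.** The article states no figure for this subgroup analysis, so there is nothing to reproduce. The check has a logical part and an illustration of size.

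**1. Who has the date.** The Sample size section gives 920 patients, allocated 2:1. Controls: 920/3 ≈ 307. CP arm: 920 × 2/3 ≈ 613. The date is undefined for all of the roughly 307 controls and for every CP-arm patient who never starts. No choice of cut-point gives a control a CP start date.

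**2. Which clock runs.** Day-28 mortality is counted from inclusion. A patient whose first CP is on day k after inclusion cannot have died before day k. A control, or a day-0 starter, can.

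**3. Illustration of guaranteed survival time.**

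Inputs:
- Mortality p = 12% to 15%, from the Sample size section: "Based on the available data, we assume 85%–88% survival in the control arm".
- Assumed, not in the article: constant hazard over 28 days, no effect of CP, and a delay of k days to first infusion.

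The share of patients dying in the first k days is 1 − (1 − p)^(k/28). For k = 2:
- p = 0.12: 1 − 0.88^(2/28) = 0.0091, and 0.0091/0.12 = 7.6% of the 28-day deaths.
- p = 0.15: 1 − 0.85^(2/28) = 0.0115, and 0.0115/0.15 = 7.7% of the 28-day deaths.

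The early deaths leave the denominator as well. Observed day-28 mortality among day-k starters is therefore 1 − (1 − p)^((28 − k)/28). Divided by p, this gives the apparent mortality ratio against all controls when CP does nothing:

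| First CP on day | p = 12% | p = 15% |
|---|---|---|
| 0 | 1.00 | 1.00 |
| 1 | 0.116/0.12 = 0.97 | 0.145/0.15 = 0.97 |
| 2 | 0.112/0.12 = 0.93 | 0.140/0.15 = 0.93 |
| 3 | 0.108/0.12 = 0.90 | 0.135/0.15 = 0.90 |

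A simulation with no CP effect and start days spread evenly over 0 to 3 (assumed) agreed. With constant hazard or with patients of unequal frailty, the ratios were about 1.00, 0.96–0.97, 0.92–0.93 and 0.88–0.90 for days 0 to 3. Between 0.7% and 1.0% of the CP arm died before starting and fell into no subgroup; with 613 patients that is about 4 to 6.

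**4. Within the CP arm.** The same figures apply to late against same-day starters, since day-0 starters have the full 28-day risk. The later group looks better with no true effect.

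**The case against.** - **The article does not say that these subgroups are compared between arms.** This stands. The item sits in a list of data to record, and the Data analysis plan section contains no such comparison. The CP start date is also natural to record for the secondary endpoints on clearance of viraemia. But the item commits the date to subgroup analyses, and a contrast within the CP arm is neither randomised nor free of the survival condition.
- **Subgroup details belong in an analysis plan that is not shown.** This is true of cut-points and models. It does not answer the point, because the difficulty lies in the variable named.
- **A reader might infer that no valid comparison by timing is possible.** The article does not support that. The same sentence names symptom onset, which precedes randomisation and exists in both arms.
- **A reader might infer that the bias would manufacture a benefit of early treatment.** Guaranteed survival time works the other way, in favour of later starters. A false early benefit would have to come from confounding, whose size cannot be derived from the article.
- **Supply and blood group may matter little.** This largely stands. Unavailable plasma and lack of an ABO-matched donor are exclusion criteria, so both should be settled before inclusion. That limits long delays and this source of confounding, although the strengths and limitations box still names the supply of matched plasma as a possible constraint.

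**Conclusion.** The point holds for any subgroup that uses the CP start date, alone or combined with symptom onset. Such a subgroup has no randomised control counterpart, and an early-versus-late contrast within the CP arm is non-randomised and tilted towards later starters.

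The size is uncertain because the article gives no delay from randomisation to first infusion. The bias from guaranteed survival is near zero if plasma starts on the day of inclusion. It is about 8% of deaths (an apparent ratio of about 0.93) for a 2-day delay, assuming constant hazard and 12–15% mortality. These figures are illustrative. The direction does not depend on the assumed delay.

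The damage is confined to a secondary analysis. The primary endpoint runs from inclusion and an intention-to-treat analysis is planned, so neither is touched. Subgroups by time from symptom onset to randomisation are sound.

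**What to change.** Replace the item with a definition that works in both arms: days from symptom onset to randomisation, with a cut fixed in advance or as a continuous term. Test it as a treatment-by-time interaction in the intention-to-treat population. State that the CP start date will be used only to describe the delay from randomisation to first infusion within the CP arm.

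The cost is one or two sentences. Symptom onset is already to be collected, and the date of inclusion must be known for every patient because the endpoint runs from it. No extra data and no change to the conduct of the trial are needed.

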**Methods and analysis:**

An open randomised controlled trial enrolling patients with COVID-19, who must be SARS-CoV-2 positive in both airway and blood samples and admitted to a study hospital. Block randomisation 2:1 is to either 200 mL CP (preferably titre ≥1/640) daily for up to 10 days (until virus negative in blood) plus standard care or standard care only (control arm). The primary endpoint is mortality by day 28 after study inclusion. Secondary endpoints include mortality by day 60 and doses of plasma needed to clear viraemia. Assuming a reduced mortality of approximately 30% by the CP therapy and 85%–88% survival in the control arm, approximately 600 participants will be enrolled to the CP therapy arm and 300 participants to the control arm.

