**Trial registration number:**

NCT04649879.

Strengths and limitations of this studyA randomised trial design based on phase I and II studies that first investigated which patients to enrol (patients with viraemia) as well as how plasma should be characterised (high-neutralising antibody titre) and how it should be given (daily until viral clearance).Powered to detect a 30% mortality decrease.Clearance of viraemia is a secondary endpoint that will be very rapid to evaluate.Availability of high-titre convalescent plasma blood group matched to study participants may be a limiting factor.This is an unblinded trial.

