### Participants

Patients with COVID-19 admitted to a study hospital will be considered for study entry. Patients will be identified by notification among doctors at the hospitals. Patients will be informed of the study and offered to participate if they match the inclusion and exclusion criteria. An electronic (REDCap, a web-based service for electronic data collection) case record form will be filled in for all screened and included patients. On inclusion, an informed consent form will be signed. Enrolment of patients is done by dedicated physicians and expected to take place during a 12-month period. Intervention is taking place up to a maximum of 10 consecutive days and follow-up will be on day 28 and day 60 after inclusion (table 1). Adherence to study protocol will be monitored by registry linkages with the patient registry.

**Table 1 T1:** Planned questionnaire and sampling follow-up

Time point (days)	Prior to or on inclusion	Daily during treatment	28	60
Informed consent	X			
CRF (Case Record Form)	X	X	X	X
Routine blood chemistry	X			
Serum sample	X	X		
Virus PCR in blood	X	X		

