### Data analysis plan

Efficacy outcomes will be determined using Cox regressions analyses, non-parametric regression analyses and survival analyses of the cohort of patients that fulfilled entry criteria but not exclusion criteria. A per-protocol and intention-to-treat analysis will be done. Final analysis will include a description of included participants, proportions of AEs and any serious AEs, the proportion of participants withdrawn or lost to follow-up, the cumulative success and failure rates by day 28 and day 60. Categorical variables will be compared using the χ^2^ test or Fisher’s exact test and continuous variables using quantile regression. The final data analysis will be performed when a total number of 88 outcome events have occurred. An interim analysis will be performed after 44 outcome events.

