## Ethics and dissemination

The trial has been registered with ClinicalTrials.gov, and sponsor protocol number CP03. The investigational product is a blood product (not classified as a drug) and the regulatory agency is the National Inspection Authority for Health and Care, which has approved the trial. The trial has been approved by the National Ethical Review Agency (decision 2020-06277). Patients will be informed of the study verbally and in writing. Details about the trial including risks and benefits will be explained and any questions answered, including the information that all participants in the study are covered by the regular patient injury insurance. A copy of the written consent form will then be signed. If an amendment substantially alters the study design, or increases the potential risk to the patients, written informed consent must be obtained again for currently enrolled patients and must be provided to additional patients prior to their entry into the study.

The trial will be conducted in compliance with the ICH (The International Council for Harmonisation of technical requirements for pharmaceuticals for human use) guidelines for Good Clinical Practice, the latest edition of the Declaration of Helsinki and any local regulations.

On inclusion, an entry will be made in the patient’s medical record specifying that the subject is participating in this study, if CP treatment is given and that written informed consent has been obtained. Any apparent side effects experienced by the subject will be assessed from the time the subject signs the informed consent and as long as the subject is part of the study, and will be reported by study site personnel either as a baseline event or an AE. The study personnel will document any baseline events or AEs in the electronic case record form (eCRF), whether observed by the investigator or reported by the subject. The safety of the different treatment arms will be assessed with regard to AEs, baseline medical conditions and findings from the physical examination and laboratory tests. All AEs, irrespective of nature, will be followed until resolution or until end of the follow-up period.

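### The daily case record form and the listed adverse-event item are tied to plasma treatment, so the open-label comparison of adverse events between arms may rest on unequal ascertainment

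*Protocol article*

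**What the plan says.** - **Arms.** Intervention: "Patients will be randomised 2:1 to treatment with CP plus standard care or standard care only". The box of strengths and limitations states: "This is an unblinded trial".
- **Schedule.** Table 1, under Participants, marks the case record form at inclusion, "Daily during treatment", day 28 and day 60. No column is defined by study day or hospital stay. The accompanying text reads: "Intervention is taking place up to a maximum of 10 consecutive days and follow-up will be on day 28 and day 60 after inclusion".
- **Adverse-event item.** Under Data collection, the one item that mentions adverse events is "Each dose of CP and date it was given along with any observed AEs".
- **Use of the data.** Outcomes lists adverse events as a secondary endpoint. The Data analysis plan will report "proportions of AEs and any serious AEs" and compare categorical variables by the χ² or Fisher's exact test. Ethics and dissemination adds: "The safety of the different treatment arms will be assessed with regard to AEs".
- **Duty and window.** Ethics and dissemination also requires side effects to be assessed in every participant from consent for as long as they remain in the study. It requires events to be entered in the eCRF whether observed or reported, and sets one reporting period from inclusion to the two-month visit. Neither the duty nor the period depends on arm.

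**The concern.** A between-arm comparison of adverse events is fair only if both arms are looked at equally often and in the same way. Here the daily form is triggered by treatment and the listed adverse-event item is paired with a plasma dose. A control patient has no plasma dose and, on the natural reading, no day in the treatment column.

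Within the plasma arm, the number of daily records also depends on how long viraemia lasts, because infusions stop once the blood is negative. The intensity of observation is therefore set partly by a post-randomisation variable.

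Mild and transient events are the ones most likely to be noted on a daily form and missed at widely spaced visits. With staff aware of allocation, this could make plasma look more harmful than it is, or leave it unclear whether an event rate exceeds background. An analysis plan cannot recover events that were never recorded, so the point belongs in the protocol.

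**Working it through.** **Step 1: scheduled recording by arm.** The plan states no adverse-event rate or capture rate, so there is no figure of its own to reproduce. The first check sets the sections side by side.

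| Element | Plasma arm | Control arm |
|---|---|---|
| Form at inclusion, day 28, day 60 (Table 1) | yes | yes |
| Daily form during treatment (Table 1) | yes, up to 10 days, ending with viraemia | undefined: no study treatment |
| Adverse-event item (Data collection) | attached to each dose | no dose to attach it to |
| Daily PCR until two negatives; days with low PaO2/FiO2 in patients not eligible for intensive care (Data collection) | yes | yes, not limited by arm |
| Adverse-event duty from consent, reporting to two months (Ethics and dissemination) | yes | yes, but no contact frequency |

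The arms differ in rows two and three. Row four gives controls some daily data, but a PCR result or an oxygenation ratio does not record adverse events. Row five fixes who is covered and for how long, but not how often anyone looks.

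**Step 2: how much unequal capture could matter.** This is an illustration only.

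Inputs from the document:
- The Sample size section gives 920 patients. Split 2:1, that is 920 × 2/3 ≈ 613 and 920 × 1/3 ≈ 307.
- The abstract's rounded version is "approximately 600 participants will be enrolled to the CP therapy arm and 300 participants to the control arm".

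Inputs assumed:
- True risk p is equal in both arms, at 20% or 30%.
- Capture is c₁ in the plasma arm and c₀ in the control arm.

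Formulas:
- Observed risks are p₁ = p·c₁ and p₀ = p·c₀, so the apparent risk ratio is c₁/c₀.
- The standard error of the difference is se = √[p₁(1−p₁)/613 + p₀(1−p₀)/307].
- The chance of a significant excess at two-sided 5% is about Φ[(p₁−p₀)/se − 1.96] with an unpooled test. It is Φ[(p₁−p₀ − 1.96·se₀)/se] with a pooled test, where se₀ uses the pooled risk.
- For the small differences in the 95%/85% case, the other tail adds less than one percentage point. It is included in the table.

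Worked case, p = 20%, capture 90% versus 60%:
- Observed risks are 0.18 and 0.12, a difference of 0.06, with se = 0.0242.
- Unpooled: 0.06/0.0242 = 2.48, and Φ(2.48 − 1.96) = Φ(0.52) ≈ 0.70.
- Pooled: the pooled risk is 0.16 and se₀ = 0.0256. Then (0.06 − 1.96 × 0.0256)/0.0242 ≈ 0.40, and Φ(0.40) ≈ 0.66.

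| True risk | Capture, plasma / control | Observed risks | Apparent risk ratio | Chance of p<0.05 (pooled to unpooled) |
|---|---|---|---|---|
| 20% | 95% / 85% | 0.190 / 0.170 | 1.12 | 11% to 12% |
| 30% | 95% / 85% | 0.285 / 0.255 | 1.12 | 16% |
| 20% | 90% / 60% | 0.180 / 0.120 | 1.50 | 66% to 70% |
| 30% | 90% / 60% | 0.270 / 0.180 | 1.50 | 87% to 89% |

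With equal capture the ratio is 1 and the chance is the nominal 5%.

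**The case against.** The case on the other side is substantial.

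- **The duty covers everyone.** Ethics and dissemination requires adverse events to be documented in every participant from consent, with one reporting period to two months. This stands. It rules out the inference that adverse-event capture as a whole depends on receiving plasma. It does not set a frequency, so the difference in scheduled observation remains.
- **Controls are not without daily data.** A reader might infer that control patients have no record at all before day 28. The document does not support that, because the daily PCR and PaO2/FiO2 items are not limited by arm. What is missing is a scheduled daily form and adverse-event entry.
- **Nothing says control events come from recall.** Controls are inpatients at enrolment, the source data are electronic medical records, and the investigator may record what is observed. So the 60% capture figure is an assumption, and retrospective capture is not established.
- **"Daily during treatment" can be read another way.** The article speaks of treatment arms, so standard care might count as treatment. That is possible. However, Intervention uses study treatment for plasma and gives standard care to those who cannot receive it, so the plasma-only reading is the more natural one. The ambiguity is itself a reason to reword.
- **This is a condensed article.** A fuller protocol may hold a visit schedule by arm. Silence alone would not be a finding. The point rests on what Table 1 and the data list state.
- **Renal events.** Table 1 schedules routine chemistry only at inclusion, so the daily column creates no scheduled difference in creatinine testing. The concern is strongest for events noted clinically.

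The primary endpoint, 28-day mortality, is not affected.

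**Conclusion.** The concern holds in a limited form. As written, Table 1 and Data collection give the plasma arm scheduled daily recording for a viraemia-dependent period and give controls no equivalent before day 28. Ethics and dissemination requires adverse events to be recorded and compared in both arms. The sections do not fit together, and in an open trial the comparison may be biased, most likely towards more recorded events with plasma.

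A reader might go further and conclude that the comparison is biased. The document does not show that: unequal capture is plausible but not demonstrated, and its size is unknown. The calculated range, from a modest distortion to a likely false signal, depends entirely on the assumed true risk and capture rates. The point is worth correcting because the remedy is a concrete and inexpensive edit to a stated schedule.

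**What to change.** Reconcile Table 1 and Data collection with Ethics and dissemination:

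1. In Table 1, define the daily case record form by days since inclusion, identically in both arms, up to a common fixed day or discharge.
2. Record adverse events on that form and separate them from the plasma-dose record.
3. Keep inclusion to two months as the adverse-event reporting period for both arms, and add a between-arm comparison within the common daily window. Restricting the comparison to the daily window alone would discard most of the reporting period.
4. Report infusion reactions separately for the plasma arm, since they have no counterpart in controls.

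The cost is an edit to the table and the data list, plus more eCRF entries for control patients, who are inpatients at enrolment with medical records available. No treatment rule changes.
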